# Promoting deceased organ and tissue donation registration in family physician waiting rooms (RegisterNow-1 trial): study protocol for a pragmatic, stepped-wedge, cluster randomized controlled registry

**DOI:** 10.1186/s13063-017-2333-5

**Published:** 2017-12-21

**Keywords:** Organ and tissue donation, Behavior change, Stepped-wedge trial, Cluster randomized trial, Organ and tissue donor registration, Protocol

## Abstract

**Background:**

There is a worldwide shortage of organs available for transplant, leading to preventable mortality associated with end-stage organ disease. While most citizens in many countries with an intent-to-donate “opt-in” system support organ donation, registration rates remain low. In Canada, most Canadians support organ donation but less than 25% in most provinces have registered their desire to donate their organs when they die. The family physician office is a promising yet underused setting in which to promote organ donor registration and address known barriers and enablers to registering for deceased organ and tissue donation. We developed a protocol to evaluate an intervention to promote registration for organ and tissue donation in family physician waiting rooms.

**Methods/design:**

This protocol describes a planned, stepped-wedge, cluster randomized registry trial in six family physician offices in Ontario, Canada to evaluate the effectiveness of reception staff providing patients with a pamphlet that addresses barriers and enablers to registration including a description of how to register for organ donation. An Internet-enabled tablet will also be provided in waiting rooms so that interested patients can register while waiting for their appointments. Family physicians and reception staff will be provided with training and/or materials to support any conversations about organ donation with their patients. Following a 2-week control period, the six offices will cross sequentially into the intervention arm in randomized sequence at 2-week intervals until all offices deliver the intervention. The primary outcome will be the proportion of patients visiting the office who are registered organ donors 7 days following their office visit. We will evaluate this outcome using routinely collected registry data from provincial administrative databases. A post-trial qualitative evaluation process will assess the experiences of reception staff and family physicians with the intervention and the stepped-wedge trial design.

**Discussion:**

Promoting registration for organ donation in family physician offices is a potentially useful strategy for increasing registration for organ donation. Increased registration may ultimately help to increase the number of organs available for transplant. The results of this trial will provide important preliminary data on the effectiveness of using family physician offices to promote registration for organ donation.

**Trial registration:**

ClinicalTrials.gov, ID: NCT03213171. Registered on 11 July 2017.

**Electronic supplementary material:**

The online version of this article (doi:10.1186/s13063-017-2333-5) contains supplementary material, which is available to authorized users.

## Background

There is a worldwide shortage of organs available for transplant. In 2013, approximately 4400 Canadians were on a waiting list for an organ transplant and 246 died waiting [1]. Many of these deaths could be prevented if more organs were available for transplant [1]. Many countries, including Canada, use an “opt-in” system, where a person can record in an electronic registry their desire to become an organ donor upon their death. The decision to donate organs ultimately falls to the decedent’s next of kin; however, knowing whether their loved one registered for organ and tissue donation can help relatives make this difficult and time-sensitive decision during the grieving period [2]. The availability of an opt-in organ donation register allows an organ donation coordinator to determine if the deceased was a registered donor before approaching their family. The coordinator can then share this information with the family member and ask if they would like to reaffirm that choice. In the province of Ontario in Canada, an estimated 90% of families consent to donation when their deceased loved one is a registered organ donor, compared to 50% who consent when the deceased had not registered [3]. Up to 90% of Canadians support organ donation; however, the proportion of Canadians actually registered is substantially lower and varies by provinces and territories [4].

In Ontario, individuals typically register for organ donation where they obtain or renew their driver’s licence or health card [5]. While prompting individuals to register at these locations is an important part of an overall strategy, given low registration rates, more opportunities to prompt members of the public to consider donor registration are needed [6]. For many reasons, the family physician office is a promising, yet underused and under-evaluated, additional setting with potential for promoting and prompting organ donor registration. Indeed, many individuals report that their family physician is a trusted source of information for organ donation and view family physician offices as an appropriate setting to obtain information about organ and tissue donation [7]. Patients are already thinking about health issues when visiting their family physician and more so relative to other settings in which organ donation might be promoted (e.g., departments of motor vehicles or large gatherings such as sporting events). Family physicians believe that discussing organ donation with their patients is within their scope of practice, although they may they lack the time to do so themselves [8]. There is also an opportunity for patients to take a few minutes to register for organ donation while waiting to see their family physician.

Several studies examining the effect of interventions to increase organ donor registration conducted in family physician settings report promising findings [6, 9–11]. Salim et al. compared the effects of a staffed kiosk containing organ donation educational material and Donor Registry Forms compared to an unstaffed kiosk in the waiting room [9]. During the unstaffed 6-week period, they found that only two patients registered over a total of 59,181 patient encounters at four clinics. During the staffed week, 102 patients registered over 9805 patient encounters. These findings emphasize that having an interpersonal component may be important in promoting organ donation registration. Bidigare et al. conducted a trial in one family practice, randomizing 300 patients to receive an information brochure or a brochure combined with a brief verbal discussion with the family physician encouraging completion of organ donor cards [10]. Thirty-three percent of patients in both arms had already committed to organ donation via driver licence stickers. Of those remaining, 40% in both arms intended to sign a donor card after the intervention, with both approaches being equally effective. Such findings suggest that while verbal discussions may be beneficial, they do not alter intentions to register for organ donation relative to a delivery method involving only a brochure. Thornton et al. conduced a randomized trial in 18 primary care offices involving 915 patients who have not yet registered for organ donation [6]. The intervention group watched a 5-min organ donation video in the waiting room and selected a question to ask their physician about organ donation (*n* = 456). The control group was consented and enrolled into the study but received usual care (*n* = 459). Intervention patients were more likely to register for organ donation (22% new registrations) compared to 15% new registrations in the control which simply involved enrolling in the study. Across all the above-mentioned studies, the emphasis has been on comparing methods of delivering intervention rather than the intervention content itself. The descriptions lacked details on the actual content of the intervention, i.e., behavior-change techniques (BCTs) delivered to address barriers and enablers to registration. Such details remain under-reported and under-specified in this academic literature leading to uncertainties in whether the reported effects are a function of any video-, brochure-, or verbal-delivery method, and/or the techniques delivered within these modalities. Further research with more detailed description is needed to facilitate the generalizability, replication and optimization of future interventions promoting organ donor registration.

### Aims and objectives

Our aim is to develop and evaluate an intervention designed to address identified key barriers and enablers to registering for organ donation. This protocol describes the development of our intervention and the design and methods that we will use to evaluate the effectiveness of our intervention in increasing organ donation registration.

Our primary objective is to evaluate whether a behavior-change, theory-based intervention developed in partnership with citizens, family physicians, and a provincial organ procurement agency delivered to six family physician offices can increase registration for deceased organ donation. The two main components of the intervention involve (1) reception staff providing unregistered patients with a pamphlet addressing barriers and enablers to organ donation registration and (2) an opportunity for immediate registration using an Internet-enabled tablet in the waiting room. Our secondary objective is to conduct a process evaluation to assess the experience of delivering the intervention from the perspective of family practice staff.

### Trial design

This is a protocol for a stepped-wedge, registry-based, cluster randomized trial conducted under real-world settings. The stepped-wedge design has the advantage of robustly evaluating the effectiveness of the intervention while also allowing all participating sites to receive the intervention. A stepped-wedge design was adopted because we suspected it to be unlikely that family physicians would agree to be randomized unless they were guaranteed, at some stage during the trial, to receive the intervention. Family physician volunteers recruited to the trial are likely to have personal connections and interests in organ donation. In a parallel arm design, being allocated to the control arm could have resulted in disappointment and may have prompted physicians to drop out of the study or adopt other interventions to promote organ donation.

The registry-based design uses routinely collected data to ascertain our outcomes. In Ontario, Canada, we have comprehensive, routinely collected healthcare administrative databases that are linked via encoded identifiers to facilitate health research (e.g., Ontario’s organ donor registry and family physician billing records). It is a cluster trial in that the unit of randomization is family physician offices (where each office may be staffed by several family physicians). Cluster randomization was used because the nature of the intervention precludes individual randomization. The order in which six family physician offices (the clusters) will receive the intervention will be randomly allocated. We used the Standard Protocol Items Recommendations for Interventional Trials (SPIRIT) Checklist to guide the reporting of our protocol (Additional file 1: Table S1) [12], the Template for Intervention Description and Replication (TIDieR) to guide the reporting of components of our intervention [13] and the Behavior Change Techniques Taxonomy version 1 (BCTTv1) to describe which BCTs we are employing in our intervention [14].

## Methods

### Participants, interventions and outcomes

#### Study setting

We will conduct the trial in six family physician offices located in Ontario, Canada. Key components of the trial are described in Table 1. As of 2008, Ontario’s organ and tissue donor registry became affirmative only (i.e., recording only “yes” responses). Citizens of 16 years of age and older can register online or can mail in a Donor Registration Form. It is also provincially mandated that individuals be asked about organ and tissue donor registration with all health-card related transactions, driver’s licence renewals and photo ID applications at ServiceOntario centers. Those who choose to register can also select to donate for research purposes and exclude certain organs or tissues from donation. While citizens can also withdraw their registration whenever they like, less than 0.1% of the registered population withdraws its registration each year.

**Table 1 Tab1:** Key characteristics of the trial

Trial characteristics	Definition
Cluster (unit of randomization)	Family physician office (a total of 6)
Number of sequences (steps)	6 (one office per sequence)
Duration of trial	14 weeks
Number of measurement periods	7 (length of each period is 2 weeks)
Individuals	Patients eligible to register for deceased organ donation and visiting a family physician at any time during the study
Timing of start of exposure	Individuals are exposed in a continuous and gradual process as they present to their family physician offices
Duration of exposure	All individuals are exposed for a short period during their visit to the physician office
Measurement	Repeated measurements are taken from mostly different individuals in each period; it is possible that a very small proportion of individuals will have repeat visits to their family doctors but because no identifying information will be collected, such individuals will be included in the analysis as independent individuals
Total number of clinics (clusters)	6

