### Sample size

We would consider an absolute increase of 10% or more in the proportion of patients who are registered organ donors at 7 days post encounter to be both clinically important and realistic to achieve. Our sample size of six clusters (10,500 patients in total) achieves 80% power to detect a 10% absolute difference assuming a control proportion of 0.5 using a two-sided test at the 5% level of significance [24]. Our calculation assumes an intracluster correlation coefficient of 0.06, as calculated from our previous work [Institute for Clinical Evaluative Sciences KDT. Feasibility of organ donor registration in family physician offices across Greater Toronto Area. Internal report: 2015; unpublished.], an average of 250 patient encounters per site in each 2-week interval, and a cluster autocorrelation coefficient of 0.8 to allow for a 20% decay in the strength of the correlation in repeated measures over time [24]. The percentage of registered donors in the control condition is conservatively assumed to be 50% to allow for a higher prevalence of registered donors in our participating offices than the provincial average. No adjustment is made for cluster attrition as the risk of attrition is extremely low, and all outcomes will be assessed from routinely collected sources, regardless of any dropout. Given some uncertainty around parameter estimates required for the stepped-wedge sample size calculation, sensitivity of our detectable effect size to a range of alternative assumptions is presented in Table 4. The results show that across a range of control arm proportions (from 0.4 to 0.5), average cluster sizes (from 100 to 400) and cluster autocorrelation coefficients (from 0.8 to 0.95), our sample size of six practices will achieve 80% power to detect absolute increases of between 5 and 11%.

**Table 4 Tab4:** Sensitivity analysis

Control proportion	Intervention proportion	Within-period ICC	Cluster autocorre-lation	Average cluster size per period	Absolute increase in proportion
0.5	0.61	0.06	0.8	100	0.110
	0.6	0.06	0.8	250	0.100
	0.59	0.06	0.8	400	0.090
	0.59	0.06	0.95	100	0.090
	0.565	0.06	0.95	250	0.065
	0.56	0.06	0.95	400	0.060
0.4	0.51	0.06	0.8	100	0.110
	0.5	0.06	0.8	250	0.100
	0.49	0.06	0.8	400	0.090
	0.49	0.06	0.95	100	0.090
	0.465	0.06	0.95	250	0.065
	0.46	0.06	0.95	400	0.060
0.45	0.56	0.06	0.8	100	0.110
	0.55	0.06	0.8	250	0.100
	0.545	0.06	0.8	400	0.095
	0.54	0.06	0.95	100	0.090
	0.515	0.06	0.95	250	0.065
	0.51	0.06	0.95	400	0.060

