### Data collection methods/data management

We will ascertain baseline and outcome information from healthcare administrative databases housed at the Institute for Clinical Evaluative Sciences (ICES). Under section 45 of Ontario’s Personal Health Information Privacy Act, ICES is considered a prescribed entity. Health information custodians, such as physicians, can disclose personal health information to ICES without patient consent for the purpose of research. These databases can be linked via encoded identifiers. Specifically, we will use our list of recruited family physicians to link to the Ontario Health Insurance Plan (OHIP) billing datasets to identify the patients who visited our recruited family physicians and the dates at which they visited. We will then use the Registered Persons Database to obtain patient demographic information and their donor registration information (including date of registration).

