### Consent, confidentiality and access to data

Only ICES personnel will have access to the patient-level dataset. Data are also encoded according to ICES policies during data analysis by the designated analyst. All donor registration results will be kept strictly confidential and no one (including the study staff) will know the registration details of any particular patient. In addition, we will not be permitted to report site-level data due to institutional policies. All study-related information will be stored securely at the researcher’s site. For the process evaluation, all participant information will be stored in locked file cabinets in areas with limited access.

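### Table 1 treats repeat visitors as separate people for a reason the linked data contradict, so one new registration can be credited to several visits, including a control visit before crossover

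*Protocol article*

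**What the plan says.** Table 1 (Study setting, Measurement row) says that mostly different people are measured in each period. It adds that "it is possible that a very small proportion of individuals will have repeat visits to their family doctors" but that, "because no identifying information will be collected, such individuals will be included in the analysis as independent individuals".

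Other sections describe data that distinguish one patient from another:

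- Trial design: the trial uses "routinely collected healthcare administrative databases that are linked via encoded identifiers to facilitate health research".
- Data collection methods/data management: billing data serve "to identify the patients who visited our recruited family physicians and the dates at which they visited". The Registered Persons Database is then used to "obtain patient demographic information and their donor registration information (including date of registration").
- Consent, confidentiality and access to data: "Only ICES personnel will have access to the patient-level dataset".

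Under Outcomes, everything is defined per patient. The primary outcome is the proportion of patients visiting in each 2-week interval who are registered 7 days after the visit. The secondary outcomes are new registrations among unregistered patients within 7 days, and also at 1, 14 and 30 days.

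Under Sample size the plan writes "Our sample size of six clusters (10,500 patients in total") and bases this on "an average of 250 patient encounters per site in each 2-week interval".

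**The concern.** Table 1 fixes an analysis rule and gives one reason for it. If the reason is false, the rule has no support, and an analysis that follows it carries an avoidable error.

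The error concerns attribution. Follow-up windows of 14 and 30 days are as long as, or longer than, the 2-week periods. If two visits by one unregistered patient are treated as two people, a single registration after the second visit can fall inside both windows. It is then counted twice. Where the office crossed over between the two visits, the control record takes credit for a registration that the intervention may have prompted. That raises the control rate and shrinks the estimated effect.

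**Working it through.** **1. Can repeat visits be recognised?** Every outcome compares a person's visit date with the same person's registration date. This needs a person-level key joining billing to registry. Two visits carrying the same encoded key are the same person, whoever that person is. The Ethics section says that individuals cannot be identified, but that concerns identity and not whether two records share a key.

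**2. The plan's total.** 6 offices × 7 periods × 250 encounters = 10,500. The number called patients is exactly the number of encounters.

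**3. Primary outcome: the plan's power, then the effect of repeats.** Inputs from Sample size: 0.50 against 0.60, two-sided 5%, ICC 0.06, cluster autocorrelation 0.8, m = 250, six sequences, seven periods.

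- Design effect for clustering: 1 + 249 × 0.06 = 15.94.
- Correlation of office-period means: r = 250 × 0.06 × 0.8 / 15.94 = 0.753.
- Stepped-wedge factor, with L = 6 steps: 3L(1 − r)(1 + Lr) / [(L² − 1)(2 + Lr)] = 0.1076.
- Individually randomised total: 776. Offices needed: 776 × 15.94 × 0.1076 / 250 = 5.3, rounded up to 6.
- Generalised least squares variance for six offices, with mean binomial variance (0.25 + 0.24)/2 = 0.245: SE 0.0335. Power = Φ(0.10/0.0335 − 1.96) ≈ 84.8%.

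This agrees with the stated 80% after rounding up. It is a normal approximation without a small-sample correction.

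The documents give no repeat fraction, so the range below is assumed. Repeats are taken to add no information, so m falls to 250 × (1 − fraction).

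| Repeat share of encounters | Non-repeat records (42 × m) | Power for 10 points |
|---|---|---|
| 0% | 10,500 | 84.8% |
| 2% | 10,290 | 84.6% |
| 10% | 9,450 | 83.9% |
| 30% | 7,350 | 81.3% |

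If instead 2% to 30% of patients recur across periods, with within-person correlation 1, the true SE is 0.998 to 0.965 of the SE that assumes independence. Ignoring that overlap is slightly conservative.

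**4. New registrations: double counting within one condition.** Assume a chance p of registering at each visit and a share r of unregistered patients who return inside the window.

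- Distinct registrants per patient: p + r(1 − p)p.
- Counted registrations: p + 2r(1 − p)p.
- Records per patient: 1 + r(1 − p).

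At p = 0.05:

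| r | Counted / distinct registrants | Records / patients | Visit-based rate | Per-patient rate |
|---|---|---|---|---|
| 0.02 | 1.02 | 1.02 | 5.09% | 5.10% |
| 0.10 | 1.09 | 1.10 | 5.43% | 5.48% |
| 0.30 | 1.22 | 1.29 | 6.11% | 6.43% |

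The counts are inflated, but numerator and denominator grow together, so the rate moves little.

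**5. New registrations: crediting across the crossover.** Here only the control numerator is inflated. Control rate as read = p0 + r(1 − p0)p1, where r is the share returning after crossover but inside the window. Assumed: p0 = 1%, p1 = 10%, so the true contrast is 9.0 points.

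| r | Control rate as read | Contrast |
|---|---|---|
| 2% | 1.2% | 8.8 points |
| 5% | 0.01 + 0.05 × 0.99 × 0.10 = 1.5% | 8.5 points |
| 10% | 2.0% | 8.0 points |
| 20% | 3.0% | 7.0 points |

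These figures apply to control visits whose window reaches past the crossover. For 14 days that is the last control fortnight of each office, 6 of the 21 control office-periods (1 + 2 + … + 6 = 21). For 30 days it is essentially the last two, 1 + 5 × 2 = 11 of 21, because the first office to cross has only one control fortnight.

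**The case against.** **The text may already mean one record per patient per fortnight.** The Table 1 sentence opens with individuals differing between periods, and both the patient eligibility criteria and the primary outcome speak of patients visiting in a period. This is a fair reading, and it removes duplicates within a fortnight. It does not remove the same person from adjacent fortnights, and the windows still cross the boundary.

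**Repeats are said to be very few.** If so, the effects are small, as the first rows of the tables show. The protocol gives no figure, however, and the linked data could supply one.

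**Index-visit rules belong in the statistical analysis plan.** Often true, and their absence alone would be no finding. Here the protocol states a rule and supports it with a reason that its own data section contradicts.

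**Stronger readings that the documents do not support.** A reader might infer that the primary result or its power is compromised; step 3 shows otherwise. A reader might also call it a miscount that registered patients leave the denominator while those who declined return to it. The first follows from defining the outcome among unregistered patients, and the second is ordinary for a rate based on visits or periods. Only crediting one registration more than once is a counting error. For the 7-day outcome that needs two visits within about a week, so it matters less there.

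**Conclusion.** The point holds in limited form. The reason in Table 1 is wrong, because the encoded linkage that the outcomes require also reveals repeat visitors, and the 10,500 patients are encounters.

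The consequence for the primary outcome is minor: power stays above 81% even at an assumed 30% of repeats. For the new-registration outcomes, mainly at 14 and 30 days, a registration can be counted more than once. The directional part is the credit given to control visits before crossover, which biases the effect towards the null. At assumed rates of 1% and 10%, it takes 0.2 to 2.0 points off a 9-point contrast as the returning share runs from 2% to 20%, for the visits within reach of the crossover. All these shares and rates are assumptions, because the documents give none. If repeats are as rare as the protocol expects, the bias lies at the low end.

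**What to change.** 1. Replace the Table 1 entry: repeat visitors are recognisable through the encoded identifier, without revealing identity.
2. Keep one record per patient per 2-week period, and state which visit in the fortnight opens the window.
3. Count each new registration once, assigned to the most recent visit on or before the registration date. Follow-up from a control visit then ends at a later intervention visit.
4. Report the observed number of repeat visitors, within and across periods.
5. Describe the 10,500 as patient encounters.

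A patient-level random effect, or restriction to the first visit in each condition, should be at most an optional sensitivity analysis. Registration is almost never withdrawn, so a patient effect on prevalence would face near-perfect within-person correlation and could be unstable under the identity link. First-visit selection would put frequent attenders into the earliest control fortnights and the first fortnights after crossover.

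The cost is a few lines of text, a little more programming and slightly fewer records. No new data are needed.
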